### Intervention description {11a}

#### mhGAP-Standard

mhGAP-Standard refers to a standardised intervention consisting of 4 in-person sessions based on the psychosocial interventions described in the WHO’s mhGAP module for substance use [15]. mhGAP is a flexible intervention guide designed to equip non-specialist providers in LMIC settings with the skills to deliver treatment for mental health and neurological conditions [14]. The intervention components are primarily focused on brief motivational interviewing, identifying triggers for use and high-risk situations, and problem-solving strategies to reduce or stop alcohol use. Participants are asked to practice skills learned in between sessions. The intervention uses a harm reduction approach, meaning that participants do not need to stop using alcohol altogether. Sessions last approximately 45–60 min each and are designed to be delivered approximately weekly, although in practice this is challenging due to scheduling difficulties and distance to the clinic. Interventionists have the option to deliver up to two additional “booster sessions” to participants who may benefit. Supplementary Table 1 provides an overview of the content covered in each session.

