#### mhGAP-Remote

Participants in mhGAP-Remote receive 1 in-person session covering the core skills of mhGAP used in the mhGAP-Standard arm, followed by standardised SMSs for a period of 8 weeks that reinforce the intervention content learned. An example SMS is, “Identify your triggers. Name a person, place, or thing that makes you want to drink alcohol. Choose one and make a plan not to interact with it this week.” SMSs are sent to participants on average twice per week at standardised days and times set by the study team. A test SMS is sent to the participant’s phone prior to them leaving the first session to ensure the phone can adequately receive SMSs and that the participant understands the delivery format. Interventionists schedule a brief check-in call with participants 2 weeks after the in-person session to ensure participants are receiving the study-related SMSs and to troubleshoot any barriers to implementing skills learned. Participants are also able to request brief telephonic support from the interventionist if they struggle to implement the skills learned by reaching out to their interventionist via SMS or phone call to request this support.

To derive the standardised SMSs used in mhGAP-Remote, formative qualitative work was conducted by the study team to gather community feedback on the content of the SMSs. SMSs were drafted based on material covered in the mhGAP psychosocial interventions for substance use. A trained member of the study team conducted in-depth interviews with 28 community members, in which they gave input on the clarity, content, and utility of each SMS. Based on this feedback, the study team (comprised of Sesotho and English speakers) adapted the content of the SMSs to improve clarity as well as to fit within the 150-character limit used by the programme sending SMSs. Additional SMSs were added after the mhGAP-Remote intervention manual was finalised, as we wanted to ensure that all important content from the in-person session was reinforced via the SMSs. These additional SMSs were reviewed as a team and changes made to ensure clarity. All SMSs underwent a forward- and backward-translation process between English and Sesotho. The final list of standardised SMSs consists of 18 SMSs. See Supplementary Table 2 for a list of the intervention SMSs and timing of delivery.

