We also plan, a priori, to conduct three separate sensitivity analyses on the primary endpoint. These are as follows:*Per protocol*. The per protocol analysis is defined as participants who attended at least one session of mhGAP-Standard or mhGAP-Remote. The per protocol analysis will allow for the evaluation of the intervention’s effects on participants who received at least a small dose of the treatment. Thus, only participants who completed at least one session of the intervention and who have an AUDIT score at the 8-week follow-up assessment will be included in this analysis. The analysis will then follow the primary analysis plan in using a linear regression model to predict difference in mean AUDIT scores from baseline to 8 weeks follow-up, using arm allocation, stratification factors, and site (if sample size allows) as independent variables.*Recovery*. If participants no longer meet the threshold of “hazardous drinking” at the 8-week follow-up assessment for alcohol use based on AUDIT score (< 6 for women, < 8 for men), they will be considered “recovered.” Otherwise, participants will be categorised as “non-recovered” because they continue to demonstrate a high burden of alcohol use symptoms. Rates of recovery will then be compared between mhGAP-Remote and mhGAP-Standard. Only participants with an AUDIT score at the 8-week follow-up assessment will be included in this analysis. For this analysis, we will employ a logistic regression model with recovery (yes/no) as the outcome and arm allocation, stratification factors, and site (if sample size allows) as independent variables.*Clinically significant and reliable change*. We will follow procedures outlined by Jacobson and Truax [47] for identifying clinically meaningful change in psychotherapy research. Means and standard deviations on the AUDIT from both clinical and non-clinical groups similar to the current population, based on a recent study in South Africa [48], will be used to establish the minimum amount of change needed that likely reflects true change in alcohol consumption (i.e., change that is not due to chance). Based on this calculation, a change of at least 8.4 points in the AUDIT score is the minimum required change. Participants would therefore need to decrease their total AUDIT score by 9 points to have clinically significant and reliable change. For this analysis, we will employ a logistic regression model with clinically significant and reliable change (yes/no) as the outcome and the same independent variables as in the primary analysis (i.e., arm allocation, stratification factors, and site [if sample size allows]).

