This trial has strengths and limitations. With regard to strengths, the study uses a randomised design to assess an innovative intervention with high potential for scale-up and evaluates the outcomes using blinded assessors. Study limitations include limited external validity based on study selection criteria, which includes individuals who have regular access to a mobile phone. Moreover, the effectiveness of mhGAP-Remote depends on successful delivery of SMSs and active engagement by participants with the messages. Prior research with an SMS-derived intervention for alcohol use reports challenges with SMS delivery [23]. The system used to deliver the SMSs in the current study can register whether the message was sent correctly, but not whether the SMS was read. As a result, measuring objective adherence to the mhGAP-Remote intervention will be limited to participant self-report.

Overall, this study will inform the effectiveness of a brief, scalable, low-resource intervention to reduce unhealthy alcohol use. This study has the potential to inform practice and policy in Lesotho and other remote, resource-constrained environments by testing a combined in-person plus SMS-based intervention that can likely reach a greater number of people with fewer human resources.

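### The 'per protocol' sensitivity set is a treatment-initiated set: one session is all of mhGAP-Remote's in-person course but a quarter of mhGAP-Standard's core course

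*Protocol article*

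**What the plan says.** The first of three planned sensitivity analyses on the primary endpoint is defined in the protocol article, Statistical methods {20a}: "The per protocol analysis is defined as participants who attended at least one session of mhGAP-Standard or mhGAP-Remote". Its stated purpose is "evaluation of the intervention’s effects on participants who received at least a small dose of the treatment". The inclusion rule follows: "only participants who completed at least one session of the intervention and who have an AUDIT score at the 8-week follow-up assessment will be included". The model is the primary one: linear regression of the AUDIT change on arm, sex, age group and, if numbers allow, site. Baseline AUDIT is not among the covariates. The Abstract also presents this analysis as one of per-protocol attendance.

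The two assigned courses differ in form. Under mhGAP-Standard: "mhGAP-Standard refers to a standardised intervention consisting of 4 in-person sessions". In addition, "Interventionists have the option to deliver up to two additional “booster sessions” to participants who may benefit". Under mhGAP-Remote: "Participants in mhGAP-Remote receive 1 in-person session covering the core skills of mhGAP". That session is followed by 18 text messages over 8 weeks, a check-in call two weeks after the session, and telephone support on request. The Discussion notes: "The system used to deliver the SMSs in the current study can register whether the message was sent correctly". It adds that reading cannot be registered.

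**The concern.** A per-protocol set is normally understood as people who received their assigned intervention broadly as planned. Here one numerical threshold is applied to two courses of different length. In Remote it is met by completing the only in-person session. In Standard it is met by starting. The rule asks nothing about later Standard sessions and nothing about Remote messages, so it does not measure adherence to the planned course in either arm.

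This matters because attendance is central to the trial's rationale. The Abstract says the need for several facility visits may limit the usual format, and the mhGAP-Standard section says weekly delivery is difficult in practice. A reader will want to know whether any advantage of Remote persists when Standard is also attended as planned. This analysis keeps every Standard participant who stopped after the first session, so it cannot answer that. Under its present label, agreement with the ITT result could be taken as an answer.

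**Working it through.** **The plan's own calculation.** The inputs, from Sample size {14}, are a difference of 2.4 points, SD 6, two-sided alpha 0.05 and power 80%. The formula is n per arm = 2 × (1.960 + 0.842)² × 6² / 2.4² = 2 × 7.85 × 6.25 = 98.1, rounded up to 99; the t-based solution is 99.08. With 20% attrition, 99 / 0.80 = 123.75, rounded up to 124 per arm and 248 in total. The stated figures reproduce, and nothing below changes them.

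**What the threshold means in each arm.** The share is the sessions needed to qualify divided by the in-person sessions planned.

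| Arm | Planned in-person sessions | Needed to qualify | Share |
|---|---|---|---|
| Remote | 1 | 1 | 1/1 = 100% |
| Standard, core course | 4 | 1 | 1/4 = 25% |
| Standard, one booster | 5 | 1 | 1/5 = 20% |
| Standard, two boosters | 6 | 1 | 1/6 = 17% |

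The 100% for Remote covers the in-person part only. Of the 18 messages, the number required to qualify is 0.

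**How mixed the Standard set could be.** The protocol gives no attendance figures, so this is an illustration under an assumption. Suppose each later Standard session is attended with probability *a*, given that the previous one was. Among those with at least one session, the share completing all four is *a*³, and the mean number attended is 1 + *a* + *a*² + *a*³.

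| *a* | Completed all 4 | Mean sessions of 4 |
|---|---|---|
| 0.70 | 34% | 2.53 |
| 0.80 | 51% | 2.95 |
| 0.90 | 73% | 3.44 |
| 0.95 | 86% | 3.71 |

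In Remote, every member of the set has completed the in-person session by definition. Even at *a* = 0.95, about one in seven of the Standard set (14%) would not have had the full core course.

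**Timing.** Participant timeline {13} allows 12 weeks after randomisation to complete sessions, but the 8-week assessment may fall anywhere from week 6 to week 16. Someone assessed at week 8 could attend a last session at week 12. A completion rule that runs to the end of the session window would then count exposure that came after the outcome.

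**The case against.** The strongest defence is that nothing is hidden. The protocol defines the set in full and says that it concerns people who had at least a small dose, and the set does that. It is one of three sensitivity analyses, and the superiority claim rests on the analysis by randomised arm. A low threshold common to both arms also limits selection after randomisation. Requiring four attendances in one arm against one in the other would select harder in Standard. All of this stands. It makes the defect one of labelling and interpretation, and it means that a stricter definition is a trade-off.

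Three stronger readings are tempting, and the protocol does not support them.

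- A reader might infer that the rule removes non-delivery from Remote. It contains no message criterion, so someone who attended the session and received no messages stays in.
- A reader might infer that the set compares a nearly complete Remote course with a partial Standard one. Remote also includes 8 weeks of messages and a call. The Discussion reports delivery problems in earlier work and says reading cannot be registered. How complete Remote treatment is within the set is therefore unknown.
- A reader might infer that incomplete Standard attendance is the hypothesised mechanism. The hypothesis is superiority only; low attrition appears in the background as a possible advantage.

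**Conclusion.** The label is wrong for what the set contains. It is a treatment-initiated set whose single threshold means the full in-person course in Remote and 25% of the core course in Standard (17% with both boosters). Agreement with the ITT result would show only that excluding people with no session changes little. It would not show that the effect holds when both courses are received as designed.

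The session shares come directly from the protocol. The completion figures of 34% to 86% rest on an assumed attendance pattern and show only how mixed the Standard set could be. Neither the direction nor the size of any shift in the AUDIT difference can be derived from the protocol. The primary analysis and the sample size of 248 are not affected.

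**What to change.** 1. Rename the set, for example initiated treatment (at least one session), in the methods section and the Abstract.
2. Report by arm the number in the set, the number excluded and the distribution of sessions attended.
3. Add baseline AUDIT to this model. It is already collected, and the groups compared are no longer protected by randomisation. It handles only that one measured difference. Fitting the model without it as well would keep the comparison with the primary analysis clean.
4. State that the set is formed after randomisation and only supports the ITT result.
5. If an analysis called per protocol is kept, specify it before unblinding, with an arm-specific definition tied to each arm's own planned course. The investigators should set the thresholds. Count only exposure before that participant's 8-week AUDIT date. For Remote, say whether sending records enter the definition, and note that they do not show that a message was read.

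Items 1 to 4 cost a few sentences, one table and one covariate. Item 5 costs more: its set would be smaller and open to selection that differs by arm, and the plan should say so.

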### Eligibility criteria {10}

#### Inclusion criteria

Participants are eligible for the study if they meet the following criteria at screening: (1) are adults (≥ 18 years old); (2) consume alcohol at a level consistent with “hazardous drinking” according to the Alcohol Use Disorders Identification Test (AUDIT) (total score of ≥ 6 for women, ≥ 8 for men); (3) have cell phone access at least half the days of the week, regular access to electricity to charge the phone, and are comfortable receiving study-specific SMSs on the phone related to alcohol use treatment; (4) willing to participate in a study focused on reducing alcohol use; (5) willing and able to regularly come to the health facility for intervention sessions during the active intervention period; (6) able to read in Sesotho or English or have a treatment supporter (e.g., family member) to read study-related materials to them; (7) willing to have the study intervention sessions audio-recorded; and (8) attends one of the study clinics and intend to remain at the same clinic for 8 months.

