#### Primary outcome

The primary outcome is mean change in self-reported alcohol use from baseline to 8 weeks follow-up (range 6–16 weeks), as measured by the continuous AUDIT score. The AUDIT is a 10-item self-report measure used extensively in LMICs to determine alcohol consumption, severity of use, symptoms of dependence, and alcohol-related problems [32, 33]. Total scores range from 0 to 40, with higher scores indicating more problematic alcohol use.

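### The 9-point rule for clinically significant and reliable change cannot be met from a baseline AUDIT of 8 or below, and its label claims more than a change-only rule can show

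*Protocol article*

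**What the plan says.** All references are to the protocol article.

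- **Rule.** Section {20a} plans three sensitivity analyses on the primary endpoint. The third starts from a derived threshold, "a change of at least 8.4 points in the AUDIT score is the minimum required change", and turns it into a whole-score rule: "Participants would therefore need to decrease their total AUDIT score by 9 points to have clinically significant and reliable change". The yes/no result goes into a logistic regression with the same covariates as the primary analysis: arm, the stratification factors and, if numbers permit, site. Baseline AUDIT is not among them, and no minimum baseline is set.
- **Entry.** The inclusion criteria require a "total score of ≥ 6 for women, ≥ 8 for men".
- **Scale.** The primary outcome section states: "Total scores range from 0 to 40".
- **End state.** The second sensitivity analysis, Recovery, classifies participants by whether the week-8 AUDIT is below 6 (women) or below 8 (men). It is separate from the 9-point rule.
- **Later visits.** Section {20a} carries both classifications to weeks 20 and 32.

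**The concern.** Two features of the rule need attention.

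First, the required drop is larger than the lowest permitted entry scores. Some participants cannot succeed whatever they do, and the plan does not say how they are handled. Three eligible scores are affected in women (6, 7 and 8) but only one in men (8), so the problem falls more heavily on women.

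Second, the outcome's name makes two claims, that the change is reliable and that it is clinically significant. The rule tests only the size of the change. The threshold is described in those terms: the reference data "will be used to establish the minimum amount of change needed that likely reflects true change in alcohol consumption". Nothing in the rule asks where the participant ends up.

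At stake is the meaning of a responder rate that readers will take as the trial's statement on clinical benefit. As written, the rate partly reflects how severe drinking was at entry, and it can call a participant clinically significantly changed while the neighbouring analysis says that hazardous drinking continues.

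**Working it through.** **Step 1. The plan's own figure.** AUDIT totals are whole numbers, so a minimum change of 8.4 becomes 9. That rounding is correct. The 8.4 itself cannot be recomputed, because the article does not print the reference means, SDs or any reliability coefficient.

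**Step 2. Can the rule be met?** The largest possible drop equals the baseline score, and the follow-up score needed is baseline − 9.

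| Baseline | Largest drop | Follow-up score needed | Attainable |
|---|---|---|---|
| 6 | 6 | −3 | no |
| 7 | 7 | −2 | no |
| 8 | 8 | −1 | no |
| 9 | 9 | 0 | only at 0 |
| 10 | 10 | 1 | yes |

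Eligibility is judged at screening, and baseline may follow up to 28 days later. If the AUDIT is repeated then, individual baselines may lie above or below the entry score. The bar at 8 applies to whichever baseline score the analysis uses.

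**Step 3. How many are affected?** The protocol gives no baseline distribution. For scale only, assume a normal distribution on whole scores with SD 6 (the pooled SD in the sample-size section), an underlying mean of 10 to 18, and truncation at the entry thresholds. The share with a baseline of 8 or below is then:

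| Underlying mean | Women | Men |
|---|---|---|
| 10 | 22.6% | 9.5% |
| 14 | 11.0% | 4.7% |
| 18 | 3.9% | 1.7% |

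Assume also that 20–40% of participants are women:

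- Highest: 0.40 × 22.6% + 0.60 × 9.5% = 14.7%.
- Lowest: 0.20 × 3.9% + 0.80 × 1.7% = 2.1%.

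This gives about 2–15% of all participants and 4–23% of women.

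**Step 4. Effect on the comparison.** If a share p in each arm cannot respond, the responder rate in each arm, and hence the risk difference, is multiplied by 1 − p. That factor is 0.85 to 0.98 overall and 0.77 to 0.96 in women. Lower response rates can also reduce the standard error, so this factor is not a direct measure of lost power.

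**Step 5. Where label and end state part company.** Recovery needs a score of 5 or less in women and 7 or less in men. A drop of exactly 9 reaches this only from a baseline of 14 or less in women (14 − 9 = 5) and 16 or less in men (16 − 9 = 7). From 15 (women) or 17 (men) upwards, a participant can meet the 9-point rule and remain non-recovered. A man falling from 30 to 21 is one example. In the other direction, a woman falling from 8 to 0 is recovered but does not count as changed.

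**The case against.** The strongest reply is that end state is not ignored. Recovery sits beside this analysis, uses the trial's own thresholds and is followed to the same visits. Separate change and end-state outcomes are bound to disagree for some participants, and reporting both loses no information on end state. That stands, and it reduces the second limb to a mismatch between name and rule. It does not remove the mismatch: the label claims clinical significance, and no planned analysis combines the two criteria.

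It is also fair to say that the unattainable cases are fixed before randomisation and so are expected to balance. Sex is both a stratification factor and a covariate. The primary outcome is the continuous change, which this rule does not touch. All of that stands. A reader might infer bias in the treatment comparison or in the primary result, and the protocol does not support that.

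A reader might also infer that 8.4 comes from the wrong inputs, or is a cut-off score mistaken for a change. The article names "Means and standard deviations on the AUDIT from both clinical and non-clinical groups similar to the current population" and mentions no reliability coefficient. That does not establish an error. The cited reference study is not at hand, and an article may condense a derivation. The figure also fits an ordinary reliable-change value: 8.4 / (1.96 × √2) = 3.03 as the standard error of measurement, which implies a reliability of 1 − (3.03/6)² = 0.745 at SD 6, or about 0.857 at SD 8. The text presents 8.4 as a change beyond chance, and nothing in it shows otherwise.

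Finally, a compound rule has its own dependence on baseline: a man starting at 30 would need to fall by 23 points to reach 7. That is a real cost, and it is why renaming the outcome is offered as an alternative below.

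**Conclusion.** The point holds in two parts. That the rule cannot be met from a baseline of 8 or below, and can be met from 9 only by reaching 0, is certain: it follows from the entry thresholds, the scale floor and the 9-point requirement. That the label overstates a change-only rule follows equally directly from the text.

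The size is less certain. The range of 2–15% of participants (4–23% of women) rests on an assumed distribution, assumed means and an assumed sex mix. The trial's baseline data will replace it.

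The consequence is limited to misclassification, some loss of sensitivity and a misleading name in one of three sensitivity analyses, repeated at weeks 20 and 32. It is worth correcting before the analysis because the correction is cheap and the responder rate is likely to be read as a statement of clinical benefit.

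**What to change.** 1. Run this analysis among participants with a baseline AUDIT of at least 9. Baseline precedes randomisation, so the subset keeps the randomised comparison. Report the number excluded by arm.
2. Add baseline AUDIT as a covariate in this model, because the room to improve still depends on the starting score above 9. This departs from the plan to reuse the primary analysis covariates and should be stated as a deliberate change.
3. Make the label match the rule, in one of two ways:
   - require both a drop of at least 9 and a follow-up AUDIT below the trial's own threshold (below 6 for women, below 8 for men); or
   - keep the 9-point rule and call the outcome reliable change.
4. Apply the same definition at weeks 8, 20 and 32.

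The cost is a few lines of analysis-plan wording and a somewhat smaller denominator. The compound rule would also give fewer responders among those analysed, with the cut-off as the stricter condition for women starting above 14 and men starting above 16. Renaming avoids that cost but leaves no analysis that combines change with end state.
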